#### Procedure for unblinding if needed {17b}

The design is open-label with only outcome assessors being blinded so unblinding will not occur.

### Data collection and management

#### Plans for assessment and collection of outcomes {18a}

The clinical investigation plan is illustrated in Fig. 4. The collection of the above-mentioned outcome data includes standardized, reliable and widely accepted methods and indices only.

#### Plans to promote participant retention and complete follow-up {18b}

An important issue in maintaining the retention of study participants is to explain the importance of prevention for individual dental health and to illustrate potential effects on medical health which are investigated in the present trial. In addition, the acceptance of basic oral hygiene measures in all participants will be ensured by remotivation.

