**Methods:**

The study has to include 120 non-smoking subjects aged between 18 and 30 years with biofilm-induced gingivitis. The chosen “waiting control group design” will compare the immediate intervention group with the delayed intervention group, which serves as a control group. Dental and gingival status, lung function and oral microbiome will be recorded. The intensified preventive intervention—professional tooth cleaning, one-stage full-mouth disinfection with CHX and safeguarding an optimal daily oral hygiene by each subject—cannot be blinded, but the outcome measurement in terms of lung function tests is blind.

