### Trial design {8}

The design of this randomized clinical trial is a “waiting control group design”, which compares the immediate intervention group with the delayed intervention group. The latter one will serve as a control group. The intervention cannot be blinded, but the outcome measure (lung function tests) is blinded, because the technician does not know to which group (immediate or delayed intervention) the subject belongs to. Moreover, the absence of any intervention in subjects with gingivitis would be unethical, but an intervention delayed for 4 weeks seems acceptable.

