### Lung function testing by spirometry

Spirometry prior to bronchodilation will be performed in line with ATS/ERS recommendations [40]. Subjects will sit while wearing nose clips, and the EasyOne Worldspirometer (ndd, Zurich, Switzerland) will be used to obtain flow-volume curves. To obtain optimal flow-volume curves, the participants perform at least three, but no more than eight, manoeuvres under the guidance of specifically trained and experienced examiners. All tests will be visually inspected by experienced physicians according to the ATS/ERS acceptability criteria [40]. Spirometric indices will be taken from the manoeuvre with the largest sum of forced expiratory volume in 1 s (FEV_1_) and forced vital capacity (FVC). Further parameters evaluated will be the ratio of FEV_1_ and FVC (FEV_1_/FVC), and the mean flow rate between 25 and 75% of FVC (FEF_25–75_). Standardized *z*-scores of the lung function parameters FEV_1_, FVC, FEV_1_/FVC and FEF_25–75_ will be calculated based on the reference equations for spirometry from the Global Lung Initiative (GLI—http://www.ers-education.org/guidelines/global-lung-function-initiative.aspx, [48]. After completion of baseline spirometry, subjects will inhale bronchodilator medication according to the ATS/ERS recommendations [40]. Two puffs (each 100 µg) of salbutamol will be delivered into a spacer (volumatic) by a metered-dose inhaler, and the participant will be asked to take five slow and deep breaths over 5–10 s for optimal deposition. Spirometry will be repeated 15 min after salbutamol inhalation. This analysis uses post-bronchodilator lung function data. A positive response is defined as an increase by > 12% and > 200 ml in FEV_1_ and/or FVC post-bronchodilation compared to pre-bronchodilation, according to ATS/ERS standards [40].

Specific attention will be paid to the requirement to obtain very precise and reliable lung function data. In addition to strictly following ATS/ERS recommendations, we will reach the goal of high-quality lung function testing by experienced and well-trained study nurses, the additional visual control by a pulmonologist and the repetition of tests for each subject. There is long-standing, well-documented expertise on lung function assessment in the investigators involved in this study.

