#### Concealment mechanism {16b}

In principle, all participants will receive the same preventive measures owing to ethical reasons. Following the allocation of all subjects to one of the intervention groups, each participant will be informed by telephone about the appointment for the phase 2 baseline examination. As the protocol for the two groups—immediate and delayed intervention—cannot be blinded for the study team and participants, no efforts will be made to conceal this information.

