### Assignment of interventions: blinding

#### Who will be blinded {17a}

The clinical research group will be blinded against the data analysts. Trial participants cannot be blinded.

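### The lung outcome is called blind because the technician is masked, but unblinded participants produce FVC by their own effort, so expectancy could bias the comparison and the retention message may add to it

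*Protocol article*

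**What the plan says.** The Abstract (Methods) says that the intervention "cannot be blinded, but the outcome measurement in terms of lung function tests is blind". Trial design {8} gives the only reason: "The intervention cannot be blinded, but the outcome measure (lung function tests) is blinded, because the technician does not know to which group" the subject belongs.

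On participants the article is open. Who will be blinded {17a} states "Trial participants cannot be blinded". Concealment mechanism {16b} says that the two-group protocol "cannot be blinded for the study team and participants, no efforts will be made to conceal this information". The same section has allocation precede the phase 2 baseline: after it, "each participant will be informed by telephone about the appointment for the phase 2 baseline examination". Procedure for unblinding {17b} adds: "The design is open-label with only outcome assessors being blinded so unblinding will not occur".

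Under Lung function testing by spirometry, each participant makes three to eight forced manoeuvres with coaching, and the indices come from the one with the largest sum of FEV1 and FVC. As a quality check, "All tests will be visually inspected by experienced physicians" against the ATS/ERS acceptability criteria.

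Under {18b}, retention rests partly on explaining the value of prevention for dental health and partly on a second message: "to illustrate potential effects on medical health which are investigated in the present trial". The limitations in the Discussion do not mention participant expectancy.

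**The concern.** Masking the technician protects coaching and recording. It does not mask the person whose inspiration and effort generate the number. The article does not call FVC effort-dependent, but this follows from the coached, forced, best-of-several procedure it describes.

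The comparator is a 4-week wait with no sham. At the comparison test the immediate arm knows it has been treated and the waiting arm knows it has not. If that knowledge changes effort even slightly, the shift would probably favour the hypothesis. Pre-post differencing does not remove a shift that differs by arm at the post-treatment test. Open allocation creates this risk; repeating the medical effect under study as a retention message may strengthen it and is avoidable.

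The second gap concerns the curve reviewers. {17b} says outcome assessors are blinded, while {16b} makes no effort to conceal the arm from the study team. The article does not say on which side of that line the inspecting physicians fall, although they judge whether tests are acceptable.

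The stake is interpretation. Objectives {7} intends to read lung function changes as direct or indirect consequences of changes in oral inflammation, and the Discussion refers to a strong design. A reader who relies on the word blind may discount an alternative explanation that the design leaves open.

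**Working it through.** **Inputs from Sample size {14}:** assumed effects of 2 and 1, so a between-arm difference of 1 unit; variance 1.5 per assessment, so variance 3 for a pre-post difference (SD √3, about 1.7); two-sided alpha 0.05; power 90%; about 60 per group.

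**The plan's own figure.** n = 2(1.960 + 1.282)² × SD² / 1².
- SD 1.7: 2 × 10.51 × 2.89 = 60.7, so 61 per group, as stated.
- Unrounded SD √3: 2 × 10.51 × 3 = 63.0, which rounds up to 64. The stated 61 therefore comes from the rounded SD.

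**Precision at 60 per group.** SE = √3 × √(2/60) = 0.316. An observed difference of 1.96 × 0.316 = 0.62 units is already significant. Power for a true difference of 1 is 88.5%.

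**Sensitivity to expectancy.** Suppose the true effect is zero and effort differs between arms by b units at the comparison. Then

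P(reject) = Φ(b/SE − 1.96) + Φ(−b/SE − 1.96).

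| b (assumed) | b/SE | P(reject) |
|---|---|---|
| 0 | 0 | 5.0% |
| 0.1 | 0.316 | 6.2% |
| 0.2 | 0.632 | 9.2% + 0.5% ≈ 10% |
| 0.25 | 0.791 | 12.4% |
| 0.4 | 1.265 | 24.3% + 0.1% ≈ 24% |
| 0.5 | 1.581 | 35% |

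**Dependence on the SD.** With the plan's alternative variance of 2 per assessment, the SD of the difference is 2 and SE = 2 × √(2/60) = 0.365. Then b = 0.4 gives b/SE = 1.095 and about 20%. With an SD of 4 (an assumption, not in the plan), SE = 0.730, b/SE = 0.548 and the rate is about 8.5%.

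**In millilitres.** The plan leaves the units open. If one unit is 1% of FVC and FVC is 4.0–5.5 L (both assumptions), the powered difference is 40–55 ml, b = 0.2 is 8–11 ml and b = 0.4 is 16–22 ml.

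**The case against.** **The open-label design is disclosed.** The sentences that call the test blind also say that the intervention cannot be blinded, and {17a} and {17b} state who is masked. This stands: nothing is hidden. The word blind for the outcome is still broader than the masking described.

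**{17b} is not wrong.** A reader might infer that it rules out accidental disclosure to the technician. It sits under the item on unblinding procedures and can be read as saying only that no code break is needed. No change is required there.

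**The retention message is not arm-specific.** It speaks of potential effects, not expected ones, and nothing restricts it to one arm. This stands. Any differential comes from open allocation; the message can only add to it.

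**The waiting arm need not expect nothing.** A reader might suppose that it does. The documents do not support this: everyone passes through a wash-in with hygiene instruction, and the sample size section itself assumes a positive change in the control group.

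**Spirometry has safeguards.** Trained examiners, up to eight attempts, acceptability criteria, pulmonologist review and repeated tests all limit submaximal effort. They do not mask the participant, and they are not designed to detect a shift of a fraction of a percent between acceptable tests.

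**The remedy is partial, and an article condenses.** Participants who undergo spirometry will probably know the lung aim whatever the retention message says, and scripts or instructions may stand in the full protocol. Both points have weight. The two texts at issue, the outcome label and the retention message, are nevertheless stated in the article.

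**Conclusion.** The point holds as a possible bias with a cheap remedy. The outcome is assessor-masked, participants are unblinded, the endpoint depends on their effort, and the limitations are silent on this. The retention message may strengthen the expectancy, and masking of the curve reviewers is left unsettled between {16b} and {17b}.

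A stronger reading would be that the bias is present, or that it is as large as the effect sought. The documents do not support either, because they contain no estimate of it. The figures of about 10% at 0.2 units and about 24% at 0.4 units are sensitivity values. They rest on a zero true effect, 60 per group and SD √3, and they fall as the SD rises; the sample size section itself says that data on variation are insufficient. They show that a small differential would matter under the plan's own assumptions, not that one will occur.

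**What to change.** - **{18b}:** base retention and remotivation on dental health only, in identical words for both arms, and do not repeat the lung hypothesis after consent.
- **Spirometry section:** instruct participants not to tell spirometry staff their arm, and have the existing physicians review curves with the arm removed. This also settles the relation between {16b} and {17b}.
- **Abstract (Methods) and Trial design {8}:** describe the lung outcome as assessor-masked with participants unblinded, instead of blind.
- **Discussion, limitations:** name participant expectancy on an effort-dependent endpoint.

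The cost is a change of wording, one instruction and coded curves for reviewers already in place, with no extra staff, visits or tests. The downside is a slightly weaker motivational message. The changes reduce the risk but cannot remove it, so the limitation is needed in any case.

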#### Data management {19}

Data management includes checks for the plausibility of all dental, spirometry data and microbiome data.

#### Confidentiality {27}

Typically, the recording of all clinical data will be handled using paper-based case report forms. The data will be digitalized immediately to make a subsequent data analysis available. All data will be collected and stored on secured university-based computers to protect confidentiality before, during and after the trial. The statutory periods of data retention will be safeguarded.

#### Plans for collection, laboratory evaluation and storage of biological specimens for genetic or molecular analysis in this trial/future use {33}

Saliva and/or gingival samples collected during each of the follow-ups will be analysed with high-throughput sequencing techniques to characterize the bacteria that are present and to determine bacterial diversity. Bacterial DNA from the 16S rRNA gene will be isolated and the V3–V4 region of the 16S rRNA amplified and sequenced by the Illumina® MiSeq platform. The resulting sequences will be assigned according to taxonomy by the Human Oral Microbiome Database (www.homd.org), which contains information of all known cultivated and sequenced bacteria in the human oral cavity. It will also be possible to apply quantitative PCR (count number of sequences) for bacteria that are identified in the output of the high-sequencing techniques to be of particular importance for gingivitis status and lung health. This will enable us to get a better estimate of the relative contribution of these bacteria in the gingival and/or saliva samples.

Quality control and advanced upstream statistical analyses will be performed in QIIME 2 and R. We will model the differential abundance of bacteria in the samples, presented by diversity indices, such as the Shannon index with the QIIME software. The Analysis of composition of microbiomes with bias correction (ANCOM-BC) methodology [33] will be used to model the differential abundance in the oral microbiome by gingivitis status and for changes in bacterial composition for repeated saliva and/or gingiva fluid samples. The false discovery rate (FDR) will be controlled at the 5% level [59] to adjust for multiple testing.

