### Biosampling and measurements of the microbiome

The secondary outcome is considered the bacterial composition. Both saliva and gingival fluid will be collected from the participants. Gingival fluid between the teeth will be collected with sterile paper points at 6 per-protocol predetermined sites in the lower jaw (mesial and distal at the “Ramfjord” teeth 41, 44 and 36) and 6 sites in the upper jaw (mesial and distal at the “Ramfjord” teeth 21, 24, 16). The samples will be frozen directly after collection, in separate vials for the upper and lower jaw samples. Saliva will be collected as well. Subjects are asked to chew for 1 min on a paraffin gum.

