## Statistical methods

### Statistical methods for primary and secondary outcomes {20a}

Processing and evaluation of data include checks for the plausibility of spirometry data and microbiome data. Moreover, descriptive data analysis will be used to check the plausibility of the distribution of data. For evaluating contextual and compositional determinants, low and high levels of outcome data will be used. In addition, potential determinants for each of the outcomes will be explored by linear regression modelling and will be checked for potential adjustment. Within these approaches, different methods of confounder adjustment (general fixed and random mixed models) will be applied for different association patterns of determinants and risk factors and for risk factor-outcome relationships in cases of clustered risk factors. For repeatedly evaluated measures throughout regression models for longitudinal data, such as the generalized estimating equations (GEE) approach may be applied.

To account for the control arm of this interventional study, multilevel statistical models can be used that integrate information on risk factor-outcome relationships on two complementary levels of intervention and non-interventional group. Such multilevel models can take confounding variables fully into account and are well-suited for studying or identifying specific group effects.

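### The microbiome analysis names contrasts by gingivitis status and over repeated samples but no between-arm contrast, and the general statistics section makes one only optional

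*Protocol article*

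**What the plan says.** Under Biosampling and measurements of the microbiome, the article states: "The secondary outcome is considered the bacterial composition". Trial design {8} describes a randomised waiting-control design "which compares the immediate intervention group with the delayed intervention group", with the control arm's treatment postponed: "an intervention delayed for 4 weeks seems acceptable".

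The only analysis text specific to the microbiome is in {33}. Diversity indices such as the Shannon index are to be computed, and ANCOM-BC "will be used to model the differential abundance in the oral microbiome by gingivitis status and for changes in bacterial composition for repeated saliva" or gingival fluid samples. Multiplicity is addressed: "The false discovery rate (FDR) will be controlled at the 5% level [59] to adjust for multiple testing". Neither arm is mentioned there. The samples are described as taken at each follow-up.

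Section {20a} is headed as covering primary and secondary outcomes, and it mentions microbiome data when describing plausibility checks. On the use of the arms it says: "To account for the control arm of this interventional study, multilevel statistical models can be used", integrating information "on two complementary levels of intervention and non-interventional group". No outcome, time point or contrast is attached to that sentence.

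Three other statements matter. The intervention includes 14 days of an antibacterial chlorhexidine rinse, and {11a} says that chlorhexidine acts on the biofilm in a dose-dependent way. All participants go through a wash-in with hygiene instruction ({13}). The Discussion suggests that the trial might contribute to causality, partly through mediation by microbiome changes.

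**The concern.** Randomisation protects one comparison, immediate against delayed intervention, during the period when only the immediate arm has been treated. Neither contrast named in {33} is that comparison.

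After randomisation, gingivitis status is something the intervention is meant to change. The same intervention delivers an agent that acts on bacteria directly. Treatment then influences both the grouping variable (status) and the outcome (abundance), so a by-status difference in post-treatment samples mixes a direct rinse effect with any real link between gingivitis and the taxon. A before-after change taken over everyone has a different weakness: it includes whatever moves in both arms, such as the response to repeated hygiene instruction.

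What is at stake is the list of taxa that the trial reports. Section {33} also foresees quantitative PCR for bacteria found to be important for gingivitis and lung health, so false leads could carry forward. A mediation argument needs, as a first step, the effect of arm on the microbiome, and the article does not commit to estimating it.

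**Working it through.** **The plan's own figure.** No sample size or power is stated for the microbiome. The only calculation is for lung function: n = 2 × (1.960 + 1.282)² × 1.7² / 1² = 60.7, so 61 per group, as stated. (With the unrounded SD of √3 it is 63.04, so 64; nothing here depends on that.) I take from it only the planned size of about 60 per arm.

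**Which contrast uses the randomised arms?**
- By gingivitis status ({33}): not randomised. After treatment starts, status is affected by arm.
- Change over repeated samples ({33}): randomised only if change is compared between arms, which the text neither says nor rules out.
- Multilevel model with an intervention level ({20a}): could be the arm comparison, but it is permissive and not tied to ANCOM-BC or to this outcome.

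**Size of the by-status bias.** Assumptions, none of them in the documents:
- one taxon on a log scale with SD 1 and no true relation to gingivitis;
- the rinse lowers it by b SD in every treated participant;
- gingivitis resolves in a proportion p₁ of the immediate arm and p₀ = 1 − p₁ of the delayed arm;
- 60 per arm, one test at p<0.05.

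Expected false difference = b × [P(treated | resolved) − P(treated | not resolved)]. With equal arms and p₁ = 0.7, p₀ = 0.3:
- P(treated | resolved) = 0.7 / (0.7 + 0.3) = 0.7
- P(treated | not resolved) = 0.3 / (0.3 + 0.7) = 0.3
- difference for b = 1: 1 × (0.7 − 0.3) = 0.40 SD

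Within each status group the variance is 1 + b² p₁(1 − p₁) = 1 + 0.21 = 1.21. The standard error is √(2 × 1.21 / 60) = 0.201 and z = 0.40 / 0.201 = 1.99, so rejection is expected in about 51% of trials. Simulation (4,000 trials per row, Welch test) agrees:

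| b (SD) | resolved, immediate vs delayed | false difference (SD) | approximate rejection | simulated |
|---|---|---|---|---|
| 0.5 | 60% vs 40% | 0.10 | 8.3% | 8.8% |
| 0.5 | 70% vs 30% | 0.20 | 18.7% | 18.6% |
| 0.5 | 80% vs 20% | 0.30 | 36.4% | 36.4% |
| 1 | 70% vs 30% | 0.40 | 51.3% | 49.5% |
| 1 | 80% vs 20% | 0.60 | 86.2% | 85.4% |

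With arm added to the model, rejection for status returned to about 5% in every row. This relies on resolution within an arm being unrelated to the taxon. Differing adherence to the rinse would break that, which is why the adjusted analysis remains observational.

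**Shared time trend.** Take a trend of 0.3 SD in both arms, no rinse effect, and within-person correlation 0.5, so that the SD of change is 1. The pooled pre-post test over 120 people has z = 0.3 × √120 = 3.29, which means rejection in about 91% of trials (simulated 90% to 91%). The same-visit comparison by status stays at 4% to 5%, and the between-arm comparison of change at about 5%. The trend therefore affects only a pooled pre-post analysis.

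**The alternative.** The between-arm comparison of change detects a 0.5 SD effect in 76% to 79% of simulated trials and a 1 SD effect in practically all, at 5% error when there is no effect.

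**The case against.** The strongest reply is that the article does not exclude an arm comparison. Section {33} concerns specimens and does not call its two contrasts exhaustive. Section {20a} covers secondary outcomes and provides for models with an intervention level. Comparing change between arms also fits the wording on repeated samples. A full protocol is said to exist, and the exact contrast may be fixed there or in an analysis plan. This stands against one inference a reader might draw, that the microbiome will not be analysed by randomised arm. The documents do not say so. It does not remove the point, because the article goes as far as naming method, contrasts and error control for this outcome and leaves out the one contrast the design was built for.

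A second reply is that gingivitis is graded. Allocation in {16a} rests on gingival health data, and the wash-in gives hygiene instruction before the professional cleaning and rinse. Status can therefore vary in samples untouched by chlorhexidine, and a by-status analysis of those is legitimate. This stands: the bias arises only if post-treatment samples are used without adjustment for arm. Sampling at each follow-up makes that possible, not certain, and the schedule figure is not available.

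A reader might also infer that rinse effects and time trends will be reported as gingivitis associations. The article does not say how results will be interpreted, and a shared trend does not distort a same-visit comparison by status.

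Finally, the percentages are single-taxon rates at p<0.05, whereas the plan controls the false discovery rate at 5% across taxa. They are not error rates of the planned procedure. False discovery rate control would change them, but it corrects for the number of tests, not for a biased contrast.

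**Conclusion.** The point holds in this form: the microbiome-specific analysis of the stated secondary outcome names no between-arm contrast, and the general section makes one only optional. The contrasts that are named lose the protection of randomisation if post-treatment samples are compared by gingivitis status without arm in the model, or if change is pooled over arms.

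The illustrated size is a false by-status difference of 0.10 to 0.60 SD, with rejection in roughly 9% to 86% of cases for a rinse effect of 0.5 to 1 SD. The effect sizes and resolution rates are assumptions, so the range shows that the bias can be material, not how large it will be here.

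This should be corrected. It concerns a secondary outcome and leaves the lung function comparison untouched.

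**What to change.** In {33}, state as the main microbiome analysis the comparison of immediate with delayed intervention in change from the phase 2 baseline to the last sample before the delayed arm is treated. Apply it to one pre-chosen diversity index and to individual taxa, with the false discovery rate held at 5% as already planned. Confirm against the schedule in Fig. 4 that samples exist at both time points.

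Keep the analyses by gingivitis status and of pooled pre-post change, but label them observational. Restrict them to samples taken before the cleaning and rinse, or adjust them for arm. Do not rest the mediation or causal statements in the Discussion on these analyses alone.

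The cost is a rewording of {33} and a matching sentence in {20a}. If the schedule already includes the two samples, no further sampling or sequencing is needed.

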## Discussion

This proposed study has several strengths: (1) It is novel, because it includes subjects with mild (and potentially reversible) oral inflammation. (2) It is innovative, because it includes oral sanitization with lung function testing and measurements of the oral microbiome. (3) It has a high public health relevance, because this study examines the potential improvement of lung function in a period of maximum achieved lung function or at least before a major decline of lung function started and has the potential to develop a strategy to counteract against lung diseases in later life. (4) It might add a piece of causality, because of the interventional aspects and mediating effects by the changes of the microbiome. (5) It is a multidisciplinary research which combines expertise on lung physiology and lung function testing with oral health and oral microbiome and epidemiological skills and statistically modelling. (6) It is a cutting-edge project, because it brings together international experts in the field from Norway (PI: [name]), with the potential to extend this interventional study to other countries. (7) It goes beyond a simple observation and hypothesis generation, because this interventional study is a proof of principle.

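### The analysis text specific to the microbiome names contrasts by gingivitis status and over repeated samples, but not the randomised contrast of immediate versus delayed intervention

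*Protocol article*

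**What the plan says.** All references are to the protocol article.

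- Under Biosampling and measurements of the microbiome: "The secondary outcome is considered the bacterial composition".
- Trial design {8} describes a randomised waiting-control design, "which compares the immediate intervention group with the delayed intervention group", with a delay of 4 weeks.
- Section {33} (biological specimens) is the only analysis text specific to the microbiome. It names QIIME 2 and R, diversity indices such as the Shannon index, and ANCOM-BC. ANCOM-BC is to "model the differential abundance in the oral microbiome by gingivitis status and for changes in bacterial composition for repeated saliva and/or gingiva fluid samples". On multiplicity: "The false discovery rate (FDR) will be controlled at the 5% level [59] to adjust for multiple testing".
- Statistical methods for primary and secondary outcomes {20a} mentions mixed models, GEE as an option for repeated measures, and this: "To account for the control arm of this interventional study, multilevel statistical models can be used that integrate information on risk factor-outcome relationships". It names microbiome data only in connection with plausibility checks.
- The Discussion lists among the study's strengths: "It might add a piece of causality, because of the interventional aspects and mediating effects by the changes of the microbiome".

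**The concern.** Section {33} specifies the software, the method, the contrasts and the error control, so the choice of contrast is something the article states and not a detail it leaves open. Neither stated contrast estimates the effect of the intervention on the flora.

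Reducing gingivitis is the purpose of the intervention (Objectives {7}). If status is measured after allocation, subjects with and without gingivitis differ in whatever made some of them respond or adhere, and the same factors may shape the flora. Randomisation does not balance these groups.

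Change over repeated samples mixes any intervention effect with the effects of time, continued hygiene instruction and study participation. Only the difference in change between the arms removes these.

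At stake are a named secondary outcome and the causal argument in the Discussion. A mediation argument first needs an effect of the randomised arm on the mediator, and section {33} names no analysis that estimates it. The lung-function comparison is not affected.

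**Working it through.** **1. The passages side by side**

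| Question | Where | Answer |
|---|---|---|
| What was randomised? | Trial design {8} | immediate versus delayed intervention |
| What is contrasted for the microbiome? | Section {33} | gingivitis status; change over repeated samples |
| Is the control arm brought in? | Section {20a} | optionally, in general terms, not tied to the microbiome |
| What is the result to support? | Discussion | mediation through microbiome changes |

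The first and second rows do not meet, and the third row allows the gap to be closed without closing it.

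**2. Before-after change, illustrated with the plan's own inputs**

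The article gives no figure for the microbiome. I borrow the inputs of Sample size {14}, which are for lung function: expected changes of 2 and 1, and an SD of each pre-post difference of √3, about 1.7.

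The plan's figure first. The formula is n per group = 2 × SD² × (z for two-sided 5% + z for 90% power)² / δ². With SD = 1.7 and δ = 1 this is 2 × 2.89 × (1.960 + 1.282)² ≈ 60.7, so 61, as stated. With the unrounded √3 it is 63.04, so 64. The rounding does not bear on this point.

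On these inputs the possible contrasts give different answers:

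- before-after change in the immediate arm: 2
- before-after change with both arms pooled: (2 + 1)/2 = 1.5
- randomised contrast: 2 − 1 = 1

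Now suppose that both arms change by 1, so that the arms do not differ. The before-after statistic is centred at 1/(√3/√n) = √(n/3).

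- One arm, n = 60: √20 = 4.47. P(significant) ≈ 1 − Φ(1.96 − 4.47) = 0.994.
- Both arms pooled, n = 120: √40 = 6.32. P(significant) is above 0.999.

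A significant change over time would therefore be nearly certain without any difference between arms. The assumption that the control arm changes is the protocol's own, but for lung function.

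**3. Contrast by gingivitis status, illustrated by simulation**

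Assumptions, none of them from the article: 60 subjects per arm; a host factor U ~ N(0,1); status after allocation = 1 if U − 0.8 × arm + noise > 0; taxon = b × U + noise; no effect of arm on the taxon. Both tests are at nominal 5%.

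| Assumed b | Rejection by status | Rejection by arm |
|---|---|---|
| 0 | about 5% | about 5% |
| 0.1 | about 8.5% | about 5% |
| 0.25 | about 30% | about 5% |
| 0.5 | about 76% | about 5% |

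The size depends entirely on b, for which the article gives no information. The direction does not: the arm comparison keeps its level throughout. The rejections by status detect a real association between status and taxon. They mislead only if read as an effect of the intervention.

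**The case against.** The strongest reply is section {20a}. It covers secondary outcomes, names mixed models and GEE, and allows multilevel models for the intervention and control groups. An arm comparison of the microbiome is therefore not excluded. This stands, and it limits the point. A reader might infer that the trial as planned cannot say whether the intervention changed the flora. The documents do not support that; they support only that no such comparison is committed to. The permission in {20a} is general, is framed around risk factors and outcomes, and does not replace the specific contrasts in {33}.

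A reader might also infer that repeated samples from one person will be treated as independent, which would give wrong standard errors and a wrong false discovery rate. The documents do not say so. Section {33} names a method without a model formula, {20a} names methods for repeated measures, and subject terms are commonly left to a fuller plan. I make no claim on this.

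The time at which gingivitis status is taken is not stated, and gingival data also exist from screening and wash-in. If the status is taken before allocation, the objection that the intervention has altered it falls away. The contrast is then a baseline association, which still does not estimate an intervention effect. Likewise, change over repeated samples could be meant as within-person change compared between arms; the text does not say this.

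Finally, Objectives {7} gives FEV1 and FEF25–75 as the secondary objective and states no microbiome hypothesis, and the Discussion's causal wording is hedged. Bacterial composition is the secondary outcome in the sense of the biosampling section. An analysis by gingivitis status is a legitimate mechanistic question. It is only not the effect of the intervention.

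**Conclusion.** The point holds in this limited form. The contrasts stated for bacterial composition are not the randomised one. By themselves they would not show whether the intervention changed the microbiome, and the general text in {20a} leaves the right comparison optional. The status contrast, if measured after allocation, is an observational association. The repeated-sample contrast, unless compared between arms, is an uncontrolled before-after change.

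The size for the microbiome is unknown. The before-after illustration (0.99 to above 0.999) rests on lung-function assumptions. The status illustration runs from about 8.5% to 76% rejection for assumed host-factor coefficients of 0.1 to 0.5, and neither end should be read as an estimate. The point is worth acting on because a named secondary outcome and a causal argument depend on it. It does not touch the primary comparison.

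**What to change.** State in section {33} or {20a} that the secondary microbiome analysis, for both the ANCOM-BC taxa and the Shannon index:

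1. compares the randomised arms on samples taken in phase 2 before the delayed group receives its intervention;
2. adjusts for the pre-intervention value, or analyses within-person change;
3. applies the 5% FDR across taxa to this arm contrast.

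Label the model by gingivitis status exploratory, and say when the status is measured.

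The cost is wording only, provided that samples are taken at the phase 2 baseline and at the end of the waiting period. Section {33} refers to sampling at each follow-up, but the schedule is in Fig. 4, which is not shown, so this should be confirmed. If a sample is missing at one of these visits, the schedule would need it added. The article reports that recruitment had not begun.
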